## Data collection and analysis

Data will be collected on case report forms (available as extended data) and stored in a secure folder on an encrypted server at the study site. Interviews will be voice recorded and transcribed on Microsoft Teams
^TM^ using HP ProBook 450 G7. Videos will be uploaded to a Microsoft Teams folder which can only be accessed by the lead researcher and fidelity assessor. Data will be anonymised and uploaded to a secure sharepoint folder. The full data management plan can be found under extended data.

Descriptive analysis of baseline characteristics will be carried out. These include CP type and body distribution, age of child, GMFCS level, previous surgery/BoNT intervention, orthotic device worn and gait aids used.

The analysis will be completed in two stages. Stage one will summarise the feasibility outcomes. Recruitment, retention and adherence rates will be reported using descriptive statistics such as percentages and 95% confidence intervals. Acceptability of the intervention and experience of the outcome measures will be described descriptively using thematic analysis of the interview transcripts. The interviews will explore any challenges or experiences based on specific participant related factors such as age or GMFCS level however as the sample size is so small it would not be possible to categorize the participants into groups based off their characteristics for the purpose of analysis.

Stage two will summarise the clinical outcomes data post intervention and 12 weeks after. As it is inappropriate to use feasibility trial data to formally test for a treatment effect, the analyses will primarily be of a descriptive nature. Interval estimates of the potential effect will be produced in the form of a 95% confidence interval and where MCIDs are reported for this population a “yes/no” will be reported if MCIDs are achieved or not. MCIDs are only reported in two measures and will not be used for power calculations. There currently is no reported MCID for the GOAL which is the primary clinical outcome measure being used for a power calculation. However, this measure was chosen by the PPI advisory groups as the most relevant to them and therefore should be considered the primary clinical outcome in a future definitive trial. A power calculation will be done on the data collected for the total score of the GOAL.

## Discussion

The MOBILE intervention has an evidence-based design and could improve walking performance in ambulant children with CP. The protocol is in keeping with the most recent recommendations for intervention design for developing motor skills
^
22
^ and includes the opinions of young people with lived experience and their parents in the design. Due to the individualised and goal-targeted design, the potential benefits of the MOBILE intervention could also include longer retention of acquired motor skills which could diminish decline in functional walking skills with age and achievement of goals to support greater participation and physical activity.

Due to the time commitment and intensity of the intervention it is important to determine how feasible and acceptable it is to carry out in a community environment, embedded in practice, to inform whether a fully powered RCT could be completed to determine its efficacy. Potential barriers to adherence could include participant fatigue or competing demands with school or hobbies. Families may find it challenging to support the participant with attending clinic appointments and completing home programs while balancing other family demands. Due to the intense nature of the intervention participants may suffer physical fatigue or muscle soreness. To mitigate the participant centred barriers, rest breaks will be provided as needed and tasks will be modified to include their hobbies where possible to increase interest and reduce mental fatigue. Where physical fatigue or muscle soreness is a barrier, mental based practice will be substituted to allow for more physical rest. To mitigate family-based barriers, appointments will be arranged to suit their schedule where possible and home programs will be incorporated into their other activities or hobbies where possible and kept simple.

The feasibility outcomes of recruitment and retention, as well as qualitative results from the interviews will inform whether a multi-site design will need to be utilised to meet the required sample size in a powered trial and facilitate participants across a larger geographical area. Adherence outcomes will inform whether a home program is sustainable alongside the clinic-based program to meet the desired total practice time and whether refinements on balance between home program and clinic sessions are needed.

This study will inform if outcome measures such as the GOAL can be used to target a meaningful walking goal, if the participants and their parents perceive the intervention to be effective and worthwhile and if any modifications or changes to the format of delivery could be made to improve feasibility. As there is scope for participants to choose an intensity and frequency schedule to suit their preferences, the interventionist will be able to reflect on their own experience of delivering the intervention in different formats to see if there is one that appears to be better tolerated by the participants and the therapist. This will inform a set frequency and intensity that can be used in an RCT design.

The upper limb MLT tool used to design the MOBILE intervention contains 21 elements and 62 strategies all of which may or may not be used in the interventions. The interventionist’s reflective diary will provide insight into the most frequently used elements and strategies for targeting lower limb tasks and will allow for further refinement of the intervention manual. A limitation in this study is the small sample size from one regional location which may lack variety in socioeconomic backgrounds or cultural variance. This could impact the variety of data collected in interviews. Another limitation is that there is only one interventionist. This will make it challenging to determine if the protocol is easy to administer with fidelity maintained by multiple therapists across different clinics as would be needed in a multi-centre RCT. Reflexive writing will be undertaken by the intervention therapist throughout the study and discussions with wider team will be done during analysis of qualitative information to limit bias.

Patient and public involvement will be used when all data is gathered to help with interpretation of results and plan for dissemination. The final study will be published in an open access peer reviewed journal and opportunities to present at conferences will be sought.

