As each participant will be targeting their own specific goal, the tasks chosen for practice will be tailored to each participants ability level and will be age appropriate. Tasks will be chosen that challenge the participant at the optimal level, provide the best motivation and are enjoyable; therefore, there will be a wide variety of tasks practiced depending on the participants intrinsic factors.

For example, a participant’s goal might be to walk faster to keep up with peers or walk without their gait aid for longer distances. The tasks will break down their gait cycle to work on improving efficiency and biomechanics. They could be first asked to analyse what they currently do and come up with ideas of how to make that better. Mirrors or video could be used to give visual feedback or directing their attention to the sound of their footsteps could be auditory feedback. Verbal feedback can be given at different time points depending on their stage of learning. They can then be encouraged through a task to analyse their performance and provide their own feedback. The tasks will be progressed with variation and translation to other tasks and ultimately will link back to the main goal.

The intervention therapist will keep a reflective diary to show how tasks were adapted based on a participants age, concentration level, motivation level, GMFCS level and walking type. Factors such as ways to introduce repetition that is fun, allowing participants choice in activities and providing variety in the environment to translate skills learnt into different scenarios will culminate in an instruction manual to support other therapists in carrying out this intervention.

To target motor skill acquisition, improvement and retention, principles of neuroplasticity are embedded in the intervention design. Neuroplasticity is the brain’s adaptive capacity to encode experiences as well as learn new behaviours and skills even after brain injury. Key elements that should be considered when designing rehabilitative therapies include; intensity and specificity of practice, salience, transference and repetition
^
32
^.

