Fidelity of the intervention will be measured using a specific measure developed and piloted by the lead researcher based on the intervention protocol. Videos of therapist led sessions will be recorded and scored using the measure by a member of the research team not involved in the intervention, who is experienced with motor learning interventions. The fidelity assessor is an Occupational Therapist who has specialised in upper limb rehabilitation at the Evelina London Children’s Hospital and was co-chair of the UK and Ireland Upper Limb Rehabilitation Network in 2019. The lead researcher will be the sole intervention therapist and is a clinical specialist physiotherapist specialising in childhood onset physical disability and has completed extra training in functional hand use in hemiplegia, bimanual therapy and was a participant in a pilot for a new online motor learning training platform. The intervention therapist will keep a reflective diary throughout the study to allow analysis of elements that could impact delivery of the intervention including equipment, facilities or intrinsic therapist qualities.

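### The therapist's reflective diary is a weak source for which elements and strategies are used most often; the independently scored session videos should supply or check this

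*Protocol article*

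**What the plan says.** The Discussion of the protocol article explains that the upper limb motor learning tool used to design MOBILE "contains 21 elements and 62 strategies all of which may or may not be used in the interventions". It then says that the interventionist's "reflective diary will provide insight into the most frequently used elements and strategies for targeting lower limb tasks", and that this "will allow for further refinement of the intervention manual".

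The Methods give the diary two other purposes:

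- Under Intervention: "The intervention therapist will keep a reflective diary to show how tasks were adapted based on a participants age, concentration level, motivation level", among other factors, leading to an instruction manual for other therapists.
- Under Fidelity of the Intervention Delivery: the diary is kept "throughout the study to allow analysis of elements that could impact delivery of the intervention including equipment, facilities or intrinsic therapist qualities".

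The same fidelity section states that "The lead researcher will be the sole intervention therapist". It also describes a second source of information about the sessions: "Videos of therapist led sessions will be recorded and scored using the measure by a member of the research team". That team member is not involved in the intervention and has experience of motor learning interventions. Fidelity itself is "measured using a specific measure developed and piloted by the lead researcher based on the intervention protocol". The checklist is listed as extended data and is not shown in the article.

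**The concern.** To say which items are used most often, one needs a numerator and a denominator: in how many of the sessions observed was each item present? As described, a reflective diary gives neither. It records what the writer thought worth noting. A strategy used in every session may be too routine to mention, while one that worked strikingly once may be described at length. Absence from the diary can mean that the strategy was not used, or that it was used and not recorded.

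The diarist is also the lead researcher, the only person delivering sessions and the author of the fidelity measure. The diary therefore offers no view of delivery independent of the study lead.

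What is at stake is the manual. It is meant to let other therapists deliver MOBILE, and the Discussion accepts that a single interventionist makes it hard to judge delivery by several therapists in a multi-centre trial. If its emphasis follows what one therapist found notable, it may differ from what the children actually received.

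**Working it through.** The article gives no frequency figure to reproduce. The check compares what the article says about each source and then asks how precise the alternative would be.

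**1. The two sources compared (protocol article)**

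| | Reflective diary | Session videos |
|---|---|---|
| Who records or scores | Lead researcher, who delivers every session | Team member not involved in the intervention |
| Purpose in Methods | Task adaptation; factors affecting delivery | Fidelity |
| Per-session record of elements and strategies | None described | Depends on the checklist, not shown |
| Given the task of showing what is used most | Yes (Discussion) | No |

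The number of items is 21 + 62 = 83. Nothing in the article links the video scores to the frequency of these items or to the manual. Data collection and analysis limits access to the videos folder to the lead researcher and the fidelity assessor. As written, the wider team could not compare the diary with the recordings.

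**2. Size of the material**

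- Planned sample (Sample size section): 12 / (1 − 0.10) = 13.3, rounded up to 14. This reproduces the stated 14.
- Sessions, for illustration: with the minimum of two a week over the full six weeks, 2 × 6 = 12 per child and 12 × 14 = 168 in all. Two a week is a minimum and six weeks a maximum, so the true number may be lower or higher.

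**3. Precision if the videos were used**

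The article does not say how many videos will be scored. Assume two per child: 2 × 14 = 28. For a strategy present in half of the scored sessions (p = 0.5, the least precise case), the 95% half-width is 1.96 × √(p(1 − p) / n_eff), where n_eff = 28 / (1 + (2 − 1) × ICC) and ICC is the assumed correlation between two sessions of the same child.

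| Assumed ICC | n_eff | Half-width |
|---|---|---|
| 0 | 28 | 1.96 × √(0.25 / 28) = 0.185 |
| 0.5 | 28 / 1.5 = 18.7 | 1.96 × √(0.25 / 18.7) = 0.227 |
| 1 | 14 | 1.96 × √(0.25 / 14) = 0.262 |

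Tasks are tailored to each child's goal, so some clustering is likely and the first row is optimistic.

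**4. Is that useful?**

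Take complete clustering (n_eff = 14) and the Wilson interval, with z² = 1.96² = 3.84. For a strategy seen in 90% of scored sessions:

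- centre = (0.9 + 3.84 / 28) / (1 + 3.84 / 14) = 1.037 / 1.274 = 0.814
- half-width = 1.96 × √(0.09 / 14 + 3.84 / (4 × 14²)) / 1.274 = 0.209 / 1.274 = 0.164
- interval: 65% to 98%

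By symmetry, a strategy seen in 10% has an interval of 2% to 35%. The two do not overlap. Strategies at 60% and 40%, by contrast, could not be told apart.

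**The case against.** The strongest reply is that the article plans no frequency analysis at all. The sentence is a forward-looking remark in the Discussion, it promises only insight, and element frequency is not among the objectives, the outcomes or the two stages of analysis. The diary is kept throughout the study. Reflexive writing and discussion with the wider team are foreseen to limit bias. The fidelity checklist is based on the intervention protocol, which is described with the same tool, so it may already record elements by session.

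Much of this stands, and it rules out several stronger readings that a reader might infer:

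- **That items will be counted from the diary.** The text does not say so.
- **That the manual will rest on selective recall.** The diary is kept as the study goes on, so the risk is selective recording. It is also not said to be the manual's only basis.
- **That these items define MOBILE, or that the therapist alone designed it.** The 83 items belong to the design tool. The article credits the evidence base and the advisory groups with shaping the intervention.
- **That the protocol calls the single interventionist the main threat to transfer.** It lists this as a further limitation, without ranking.
- **That video is free of bias.** Only therapist-led sessions are filmed, up to 20% of practice may be unsupervised, and the lead researcher wrote the scoring measure.

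The core is not answered. The article names a source for what is used most often, and that source does not suit the statement. Reflexive writing and team discussion can temper interpretation, but they do not produce a count. If the checklist does record elements, the article still does not direct its results to this question, and the remedy becomes easier.

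**Conclusion.** The point holds in a limited form. The Discussion relies on the sole therapist's diary for a statement about frequency across 83 items, and the diary as described cannot separate non-use from unrecorded use. A more suitable and more independent source is already planned and is not assigned to the task.

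The size of any distortion cannot be calculated from the article. The gain from the alternative can be sketched: about ±19 to ±26 percentage points at a frequency of one half, assuming two scored videos for each of 14 children and clustering between none and complete. That is modest, but it separates widely used strategies from rare ones.

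The consequence is confined to refinement of the manual. Recruitment, adherence and retention rates, the clinical estimates and the power calculation on the GOAL do not depend on it. It is worth correcting because the remedy is cheap, but it does not threaten the study's main results.

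**What to change.** In the Discussion, and preferably also under Fidelity of the Intervention Delivery:

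1. State that the frequency of elements and strategies will be taken from, or checked against, the independently scored videos. Use the fidelity checklist if it already records them; otherwise add a short tick list for the same assessor.
2. Report each item as the percentage of scored sessions and the percentage of children in which it was seen, with the number of sessions scored.
3. Have someone other than the therapist choose the sessions to be scored, in advance; for example, one early and one late session per child.
4. Keep the diary for what the Methods intend: explaining how and why tasks were adapted and what affected delivery.
5. Say that the frequencies describe therapist-led practice only, and give them with intervals.

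The cost is some additional scoring time for the existing assessor. No new staff, visits or recordings are needed.

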## Ethical considerations

Ethical approval has been granted through Enable Ireland and the Royal College of Surgeons Ireland Research Ethics Committees.

Enable Ireland Research Ethics and Quality Committee (REQC) approval received on 17
^th^ of June 2024. Reference Number: RA96

Royal College of Surgeons Research Ethics Committee approval received on the 5
^th^ of March 2024. Reference Number: REC202312001

This study adheres to the Declaration of Helsinki for studies involving human subjects
^
43
^

Explicit, informed, written consent will be obtained from the parent/guardian of each participant. Written assent will also be obtained from each participant. Should a participant turn 18 during the study they will be asked to complete an updated informed written consent.

Participants will be informed of their right to withdraw at any stage without affecting their usual care. Both ethics committees will be informed of any changes to protocol via respective revision procedures.

## Protocol version control

**Table T1:** 

Version 1	30/06/2023	
Version 1.2	27/04/2024	Intervention Manual format change from Tidier Checklist to template for upper limb motor learning strategy tool. Change to frequency and intensity options for intervention provided based on PPI advisory panels.
Version 1.2.1	09/08/2024	Recruitment strategy expanded to include participants accessing motor management services in Enable Ireland to allow for greater diversity in sample. Primary clinical outcome measure for power calculation changed from 6minute walk test to Gait Outcome Assessment List following discussions with advisory group.
Version 1.2.2	27/02/2025	Updates to background information with evidence from new systematic review added. More detail added to study limitations and discussion.
Version 2	26/01/2026	Extra detail provided in all sections based on reviewer comments and addition of assent form to extended data.

## Data Availability

No data are associated with this article. Figshare: TIDieR Description MOBILE.
https://doi.org/10.6084/m9.figshare.28524953
^
44
^. Figshare: MOBILE Protocol.
https://doi.org/10.6084/m9.figshare.28524788
^
45
^. Figshare: MOBILE Fidelity Checklist.
https://doi.org/10.6084/m9.figshare.28524764
^
46
^. Figshare: Data Management Plan.
https://doi.org/10.6084/m9.figshare.28524650
^
47
^. Figshare: Patient Information Leaflet.
https://doi.org/10.6084/m9.figshare.28524803
^
48
^. Figshare: Consent Form.
https://doi.org/10.6084/m9.figshare.28524830
^
49
^. Figshare: Case Report Form.
https://doi.org/10.6084/m9.figshare.28525043
^
50
^. Figshare: WHO Trial Registration Data Set.
https://doi.org/10.6084/m9.figshare.28533185
^
51
^. Figshare: Assent Form.
https://doi.org/10.6084/m9.figshare.30343585.v1
^
52
^. Data are available under the terms of the
Creative Commons Attribution 4.0 International license (CC-BY 4.0). Figshare: SPIRIT checklist for ‘A "motor learning-based intervention for lower extremities (MOBILE)" to target walking performance in ambulant children with cerebral palsy: A feasibility study’.
https://doi.org/10.6084/m9.figshare.28525082
^
53
^. Data are available under the terms of the Creative Commons Attribution 4.0 International license (CC-BY 4.0).
